### Statistical methods

There have been no previous studies investigating the effect of istradefylline treatment on the flexibility of the doses of levodopa-containing formulations. Thus, we used real-world data based on information from the medical claims database (Medical Data Vision Co., Ltd., Tokyo, Japan) to estimate the between-group difference in the Mann–Whitney U test by simulating cumulative L-DOPA doses in PD patients (non-istradefylline treatment), which would ensure a power of 80% with groups of 50 patients. In this condition, an approximate 21.3% in between-group difference over a period of 9 months (270 days) is detectable as the area under the curve (AUC) of cumulative additional L-DOPA doses between treatments (data on file; Kyowa Kirin Co., Ltd., Tokyo, Japan). Based on the mean additional levodopa dose over 9 months (approximately 265 mg) in a previously published study [36], recommendation from the Expert Medical Advisory board for this study, and the clinical experience in Japan, we anticipated that istradefylline might suppress the dose increase of levodopa-containing medications by 20%. Therefore, the sample size was set at 111 patients, to allow for 10% drop-outs and to ensure that there were 50 patients per group with data evaluable for the efficacy analyses.

The efficacy and safety analysis sets will include all patients who meet the inclusion criteria and do not meet the exclusion criteria, with the exception of those who withdraw consent before the start of the observation period (Week 0) or are withdrawn by the study investigator, and those randomly assigned to istradefylline treatment but who do not start administration of istradefylline. The patient background data that will be collected will include date of birth (if not disclosed, age at the date of consent), sex, height, weight, caregiver availability, pregnancy, hospitalization, year of onset of PD, year of onset of wearing-off, family history of PD, year of initial treatment with levodopa, daily dose and number of administrations of levodopa, levodopa equivalent dose, MMSE score, and mH&Y (ON/OFF).

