Summary statistics will be calculated for quantitative variables, and the number of patients and percentage will be determined for categorical variables. For the primary endpoint, the cumulative additional levodopa dose (AUC during the treatment period) will be calculated using the Mann–Whitney U test. The cumulative additional dose (AUC of additional dose during the treatment period) will be calculated as the total dose (daily dose × number of days) added to the dose of levodopa-containing medications (300–400 mg/day) at randomization. For the secondary endpoints, the cumulative additional doses of levodopa will be calculated for the patients who completed the treatment (Week 37). A log-rank test will be performed on the number of days from the start of observation (Week 0) to the time of dose increase, and time-to-event curves will be created using the Kaplan–Meier method. Summary statistics of the secondary endpoints at each observation time point will be calculated for each group, and mean and standard deviation data will be plotted in a line graph. Scores at each time point will be compared between groups using the Mann–Whitney U test. Correlation of the secondary endpoint scores will be performed using the Spearman correlation coefficient, and scatter plots will be created. A two-sided significance level of 5% will be applied to between-group comparisons, and two-sided 95% confidence intervals will be calculated. No imputation will be made for missing data. We will prepare a detailed statistical analysis plan before the database is finalized and locked. Statistical analyses will be conducted using SAS version 9.4 (SAS Institute Inc., Cary, NC, USA).

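### Secondary scales are tested visit by visit without baseline adjustment or a designated visit, which gives up precision and leaves 57 to 105 tests at 5%

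*Protocol article*

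**What the plan says.** In the protocol article, Statistical methods, the rule for the secondary scales is "Scores at each time point will be compared between groups using the Mann–Whitney U test". The same paragraph sets the level, "A two-sided significance level of 5% will be applied to between-group comparisons", and plans 95% confidence intervals alongside. On incomplete data it says "No imputation will be made for missing data". It names no covariate, no repeated-measures model and no main visit for any secondary scale. A detailed analysis plan is promised before database lock.

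The section Efficacy outcomes lists three kinds of by-visit comparison:
- score and change for CGI-S, PGI-S, mH&Y (ON and OFF), MDS-UPDRS parts I to IV and PDQ-39;
- score only for CGI-I and PGI-I;
- the added levodopa dose at every visit from Week 4 to Week 36.

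Table 1 schedules a Week 0 value for every scale in the first group. Its footnote b lets the Week 36 column also stand for the visit made when a patient discontinues. Allocation is by minimisation on age, levodopa equivalent dose and dyskinesia. The primary endpoint is a separate, single Mann–Whitney test of cumulative additional dose.

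**The concern.** A lower cumulative levodopa dose supports a sparing effect only if symptoms were not worse in the arm that received less. The secondary scales carry that evidence. With about 50 evaluable patients per arm, the estimate for each scale should be as precise as the data allow, and the reader should know in advance which estimate to look at.

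The named test does neither. It does not use the Week 0 value as a covariate, so variation between patients that was present before treatment stays in the comparison. The protocol's Limitations section itself warns of chance imbalance between small groups of heterogeneous patients, and baseline adjustment would deal with that scale by scale. Each scale also produces several p-values with none marked as its result, so an isolated value below 0.05 has no clear meaning. Finally, an unadjusted test of the values available at a visit makes no use of a patient's earlier scores, which may predict who leaves.

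**Working it through.** **The plan's own figures.** The protocol states "which would ensure a power of 80% with groups of 50 patients", "the sample size was set at 111 patients" and "to allow for 10% drop-outs". Two groups of 50 make 100, and 100 / 0.9 = 111.1, so the total of 111 is reproduced to within one patient. The 21.3% detectable difference concerns the primary endpoint and cannot be rebuilt, because its standard deviation is in data on file.

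**1. Count of tests** (Table 1 and Efficacy outcomes; post-baseline visits only)

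| Item | Visits | Score tests | Change tests |
|---|---|---|---|
| CGI-S | 9 | 9 | 9 |
| PGI-S | 9 | 9 | 9 |
| mH&Y ON, OFF | 3 | 6 | 6 |
| MDS-UPDRS I–IV | 3 | 12 | 12 |
| PDQ-39 | 3 | 3 | 3 |
| CGI-I, PGI-I | 9 | 18 | none |
| Total | | 57 | 39 |

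Scores alone: 57. With changes: 57 + 39 = 96. With the 9 per-visit dose comparisons: 96 + 9 = 105.

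Expected false positives if every null is true: 57 × 0.05 = 2.85; 96 × 0.05 = 4.8; 105 × 0.05 = 5.25. The chance of at least one is 94.6%, 99.3% and 99.5% if the tests were independent. They are not. A simulation of 105 correlated Mann–Whitney tests (50 per arm, assumed correlation 0.6 to 0.8 within a scale and 0 to 0.5 between scales) gave 92% to 97%.

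**2. Precision.** The correlation r between baseline and follow-up score is not in the document; r = 0.3 to 0.8 is assumed. With equal variances at both times, the variance of the arm difference relative to the raw score is:
- raw score: 1
- change score: 2(1 − r)
- baseline-adjusted: 1 − r²
- adjusted relative to change: (1 − r²) / [2(1 − r)] = (1 + r) / 2

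| r | Change | Adjusted | Adjusted / change |
|---|---|---|---|
| 0.3 | 1.40 | 0.91 | 0.65 |
| 0.6 | 0.80 | 0.64 | 0.80 |
| 0.8 | 0.40 | 0.36 | 0.90 |

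For scale: with 50 per arm, two-sided 5% and 80% power, the detectable standardized difference is (1.960 + 0.842) × √(2/50) = 0.56 for a comparison of means. For Mann–Whitney it is 0.56 / √0.955 = 0.57, where 0.955 is the asymptotic efficiency for normal data. With adjustment at r = 0.6 it is 0.56 × √0.64 = 0.45 (0.53 to 0.34 over the range of r). At a true difference of 0.5 SD, power is 69% for Mann–Whitney on the score, 78% (54% to 97%) on the change and 88% (75% to 99%) with adjustment.

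**3. Dropout.** Simulation of the difference in observed means at Week 36, with 56 per arm, r = 0.6 between all visits and a true Week 36 effect of 0.50 SD:
- Dropout depends on the previous score in the same way in both arms (12% and 9% lost): observed-case difference 0.48; adjusted for baseline 0.49.
- Dropout depends on the previous score in the control arm only (12% against 5% lost): 0.41, about 20% too small; adjusted for baseline 0.46.

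**4. After the change.** One main result per scale leaves 7 results (CGI-S, PGI-S, MDS-UPDRS I–IV, PDQ-39), or 9 with mH&Y ON and OFF. Expected false positives under the null are then 7 × 0.05 = 0.35 to 9 × 0.05 = 0.45.

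**The case against.** The strongest reply is that these are secondary analyses, a detailed analysis plan is promised, and a main visit or covariates are commonly left to it. That would answer a complaint about missing detail. It does not answer this one, because the article names the test, the level and the missing-data rule, and the analysis plan would have to depart from them.

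Several stronger readings are tempting and are not supported:
- **Baseline is ignored.** It is not, since changes in score are also compared. Change remains less efficient than adjustment at every r below 1, but at r = 0.8 the gain over change is only 10% of the variance.
- **There are 105 tests of scores.** The quoted sentence covers 57. Changes are added from the endpoint list, and 9 of the 105 concern dose.
- **Only patients still in the study contribute.** Footnote b of Table 1 schedules a final assessment for those who discontinue. The article does not say how these values enter the Week 36 comparison.
- **Dropout biases the results.** At the planned 10% the bias is small unless the mechanism differs by arm. That is possible in an open-label trial, but nothing in the document shows it.
- **The trial's false-positive rate is inflated.** The primary endpoint is one separate test, and the secondary tests are not called confirmatory.

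It is also fair to say that the output is not p-values alone: summary statistics, plots and 95% confidence intervals are planned. The variance factors describe linear comparisons of means and carry over only roughly to rank tests on ordinal scales.

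**Conclusion.** The point stands as one of efficiency and interpretability for the secondary scales. The specified analysis gives up precision that the Week 0 data already offer: 9% to 64% of the raw-score variance and 35% to 10% of the change-score variance, for an assumed r of 0.3 to 0.8. It also yields 57 to 105 tests at 5% with no visit designated, so 2.9 to 5.25 false positives are expected if every null holds. The harm is to how the secondary results can be read. The gain in precision rests on the assumed correlation and on a linear-model approximation, and the dropout figures rest on the simulated mechanisms. The change is cheap and worth making before database lock.

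**What to change.** In the analysis plan:

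1. For MDS-UPDRS parts I–IV and PDQ-39, fit a mixed model for repeated measures (Weeks 12, 24 and 36) with arm × visit, baseline × visit and the three minimisation factors. Report the adjusted Week 36 difference with its 95% confidence interval as that scale's main result. The model uses the available visits under a missing-at-random assumption, so the rule against imputation can stay.
2. Assign assessments made on discontinuation (Table 1, footnote b) to the time at which they were made, not to Week 36.
3. For CGI-S, PGI-S and mH&Y (ON and OFF), use a baseline-adjusted ordinal or rank analysis at Week 36, for example a proportional-odds model reporting an odds ratio, or rank ANCOVA. Simplify it if categories are sparse. A repeated cumulative-logit model with visit interactions may not converge in about 100 patients and is not needed.
4. Keep all by-visit Mann–Whitney results, including CGI-I and PGI-I, which have no Week 0 value, as descriptive and without claims of significance.

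The cost is some model assumptions, for which the retained rank tests give a check, and a little more analysis work in standard SAS procedures. No extra patients, visits or data are required.

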## Discussion

The ISTRA ADJUST PD randomized, controlled, open-label study is designed to address several key questions in the treatment of PD patients. At the end of the study, the study data will be published in academic meetings or journals in Japan and globally, and it is expected that the results will add to the available knowledge base and help to inform future clinical decision-making. It is imperative that clinicians have access to robust data examining the impact of different treatment options in patients experiencing the wearing-off phenomenon. Primarily, our study intends to identify whether the administration of istradefylline has any effect on the cumulative additional dose of levodopa-containing medications, thereby providing indirect evidence for levodopa-sparing. In addition to the treatment effect of istradefylline on the symptoms of wearing-off, we will also examine whether the administration of adjunctive istradefylline has any effect on the final dose of levodopa-containing medications; this will help to inform future treatment decisions for PD patients using istradefylline.

Previous publications have suggested that the daily dose of levodopa may be predictive of treatment-induced dyskinesia [11, 37–39], with the risk of motor complications increasing with doses above 400 mg/day [10]. Therefore, in this study, we will evaluate the effect of istradefylline on dose escalation from the daily levodopa dose of 300–400 mg, which requires careful judgment. We anticipate that the results obtained will be of immense practical use to physicians in assessing routine clinical issues associated with dose escalation above 400 mg/day. As the clinical benefits and adverse effects may be difficult to balance in patients with advanced PD, it is considered necessary that the levodopa dose modifications are made in small increments; thus, each dose escalation in this study was set to 50 mg.

There is considerable interest in a personalized approach to PD treatment [40–42], largely due to the clinical heterogeneity observed amongst patients. However, for this approach to be successful, there must be a clearer understanding of the associations between different subjective and objective measures of PD symptoms and the therapeutic outcomes. In this study, we intend to evaluate whether there is any relationship between the change in the index used to determine the dose increase of levodopa-containing medications (CGI-S) and the change in other indicators (CGI-I, PGI-I, PGI-S, CGI-S, mH&Y, MDS-UPDRS parts I–IV, PDQ-39, and data from the wearable device). The CGI was chosen as the criterion for increasing the levodopa dose as this reflects the routine clinical measure by which physicians judge dose adjustment; thus, by investigating the correlation between CGI and the other specified indicators, we can ascertain the objectivity of the CGI as a tool for therapeutic decision-making.

Finally, more severe dyskinesia is known to have a negative impact on patient quality of life (QOL) [43–45]. By identifying a therapy that reduces the levodopa dose and the risk of complications associated with levodopa-containing medications, studies such as this can contribute considerably to improving the QOL of PD patients and their families/caregivers. We believe that this study will provide a much-needed source of additional information, which can be used to underpin future treatment recommendations and practice to improve not only objective motor and non-motor symptoms, but also subjective and objective QOL, for the benefit of real-world PD patients.

### Limitations

We acknowledge that our study has several limitations, of which the most notable is the open-label design. However, the inclusion of objective measures using the wearable device is intended to offset any bias resulting from the open-label study design and unblinded knowledge of the drug regimen administered. Moreover, the study aims to evaluate the levodopa-sparing effect; however, due to the ethical feasibility issue for patients, the study is designed to evaluate additional levodopa dosage. We also note that any conclusions resulting from our analysis must be made with caution, since we are unable to exclude the effects of PD drugs other than levodopa, and the short (37-week) observation period precludes long-term evaluations of effects in this chronic disorder. Because of the heterogeneity of PD and the small number of study participants, there is a risk of bias as some subtypes may be over-represented in one group over the other. The average timing for additional administration of levodopa remains unclear; thus, a 37-week observational period might not be sufficient to detect changes in levodopa requirements. However, in a previous randomized controlled study [36], the levodopa dose at 9 months increased to approximately 265 mg. This was a levodopa-controlled, flexible-dose study, similar to the current study, and the average levodopa doses at baseline between the studies are comparable. Therefore, we believe that the 37-week observation period will be enough to detect changes in levodopa requirements. Finally, we recognize that the lack of a pathologically confirmed diagnosis may lower the accuracy of the PD diagnosis. Nonetheless, we feel that any confounding effect is likely to be small, given that eligible patients must have had PD diagnosed using standardized, international MDS criteria and have been receiving treatment for PD prior to enrolment.

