### Study design, treatments, and blinding

The ISTRA ADJUST PD study is a multicenter, randomized, open-label, parallel-group controlled study (Fig. 1). Study participants will be randomly assigned to either the istradefylline group or the control group in a 1:1 ratio. Randomization will be centrally performed via computer allocation, using a minimization method and stratified according to age (< 60 or ≥ 60 years), levodopa equivalent dose (< 400 or ≥ 400 mg/day), and dyskinesia (presence or absence). The study will be conducted from February 2019 to February 2022 (with the registration period lasting until November 2020), and the expected duration of involvement for each participant is 37 weeks. The observation schedule is shown in Table 1; most observations will be conducted at 4- or 12-weekly intervals during the study period.

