The criteria for the titration of levodopa-containing medications are as follows: if the clinical global impression of severity scale (CGI-S) is ≥ 4 on the day of observation, the dose is incrementally increased by 50 mg/day. If an intolerable adverse reaction occurs due to the dose increase, reduction of the dose of the levodopa-containing medication is allowed (at the physician’s discretion; no reduction amount is specified). For levodopa, only a dose increase of 50 mg/day per visit will be allowed.

Once-daily oral administration of a 20 mg istradefylline tablet will be started at Week 0. At Week 1, if the treatment is well tolerated and motor symptoms persist, the dosage of istradefylline will be increased to 40 mg, once daily. Dose reduction is allowed if treatment is not tolerable.

Changes in the dosage and dosing regimen of anti-PD drugs are not permitted within 4 weeks before enrollment and during the treatment period. However, dose reduction of a specific drug is permitted, if intolerable adverse reactions causally associated with that drug appear.

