### Efficacy outcomes

The primary study endpoint is the comparison of the cumulative additional dose of levodopa-containing medications during the treatment period (from Week 0 to Week 37) between patients with PD who receive adjunctive istradefylline and those who do not.

Secondary efficacy endpoints are the between-group comparisons of additional levodopa doses on each observation day from Week 4 to Week 36; the number of days until the first dose increase after Week 4; change in dose of levodopa-containing medications until Week 36; CGI-S score and change in score; CGI-improvement scale (CGI-I) score (to measure the degree of improvement from the previous evaluation); patient global impression of severity (PGI-S) score and change in score; PGI-improvement (PGI-I) score (to measure the degree of improvement from the previous evaluation); mH&Y staging scale (ON/OFF) score and change in score; MDS-UPDRS part I score (nonmotor experiences of daily living), part II score (motor experiences of daily living), part III score (motor examination), part IV score (motor complications), and change in scores; Parkinson’s Disease Questionnaire-39 (PDQ-39) score and change in score; and correlations between any of the score changes. Correlations between CGI-S and other measures (e.g., MDS-UPDRS3, MDS-UPDRS4, and PGI-S) will be evaluated to confirm whether dose escalation decisions would differ between using CGI-S and using other measures.

Patients will also wear a wristband-type triaxial accelerometry system (UW-301BT, Hitachi Systems Ltd., Tokyo, Japan) on their non-dominant wrist for 7 days every 3 months during the study; data extracted from the wearable device will include movement frequency and intensity, gait (step count, pace, and laterality), and sleep (bedtime, awakening time, duration of sleep, sleep efficiency, sleep onset latency, movement during sleep, and number of episodes of getting out of bed).

Safety endpoints for this study will include adverse events and adverse drug reactions classified based on System Organ Class and Preferred Term defined in the Medical Dictionary for Regulatory Activities (Japan edition), using the most recent version at the time of coding.

Exploratory endpoints include evaluation of the correlation between the information extracted from the wearable device and the primary/secondary efficacy endpoints.

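### The wearable data do not offset open-label bias in the primary endpoint, and the Spearman correlations named cannot show whether dose decisions would differ at the CGI-S threshold

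*Protocol article*

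**What the plan says.** All references are to the protocol article.

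- **Dose rule** (titration criteria after Table 1, in Study design, treatments, and blinding): if the "clinical global impression of severity scale (CGI-S) is ≥ 4 on the day of observation, the dose is incrementally increased by 50 mg/day". The trial is open-label and no blinded rater is described.
- **Primary analysis** (Statistical methods): "the cumulative additional levodopa dose (AUC during the treatment period) will be calculated using the Mann–Whitney U test". The AUC accumulates the increments that the CGI-S rule produces.
- **Open-label bias** (Limitations): the design is named as the most notable limitation, followed by the statement that "the inclusion of objective measures using the wearable device is intended to offset any bias resulting from the open-label study design".
- **Wearable analysis** (Efficacy outcomes): "Exploratory endpoints include evaluation of the correlation between the information extracted from the wearable device and the primary/secondary efficacy endpoints". The device is worn for 7 days every 3 months.
- **CGI-S as dosing index** (Efficacy outcomes): correlations of CGI-S with measures such as MDS-UPDRS parts III and IV and PGI-S "will be evaluated to confirm whether dose escalation decisions would differ between using CGI-S and using other measures". Statistical methods fixes the tool: "Correlation of the secondary endpoint scores will be performed using the Spearman correlation coefficient", with scatter plots. The Discussion expects these correlations to establish how objective the CGI is for treatment decisions.

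**The concern.** A physician who knows the arm scores CGI-S, and that score crossing 4 generates the primary endpoint. If physicians score patients on istradefylline slightly lower for the same severity, fewer increments follow and the AUC falls without any drug effect.

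The protocol offers two reassurances, and neither matches its purpose. The wearable is said to offset the bias, but it plays no part in the dose rule or the primary comparison. The correlations are said to show whether dose decisions would differ, but dose decisions turn on a cut-point and a rank correlation does not measure agreement at one. A reader who sees respectable coefficients could take the primary result as protected against rating bias when the analysis had not tested for it.

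**Working it through.** **1. The plan's own figures.** 100 evaluable patients with 10% drop-out: 100/0.9 = 111.1, against the stated 111 (112 if rounded up). This reproduces. The 21.3% detectable difference at 80% power cannot be rebuilt, because the AUC distribution is data on file. The benchmark below is the anticipated 20% suppression.

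**2. Where each measure enters.** CGI-S is rated at nine dose decisions (Weeks 4 to 36, every 4 weeks) and feeds the AUC directly. The wearable is recorded at enrolment and around Weeks 12, 24 and 36 (Table 1). It feeds neither the rule nor the AUC.

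**3. Threshold against rank.** Assumptions, none in the documents: underlying CGI-S mean 3.5 and SD 0.9, scores rounded, so that a score of 4 or more means an underlying value of at least 3.5. With a downward shift s in one arm, the share of visits at or above 4 is 1 − Φ(s/0.9).

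- s = 0: 50%.
- s = 0.25: 1 − Φ(0.278) = 39.1%, a relative drop of 1 − 39.1/50 = 22% (simulated 39.2%).
- s = 0.5: 1 − Φ(0.556) = 28.9% (simulated 29.0%).

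Pooled Spearman's rho between CGI-S and a reference measure, before and after the 0.25-point shift in one arm:

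| Assumed reference correlation | No shift | Shift 0.25 |
|---|---|---|
| 0.3 | 0.275 | 0.275 |
| 0.6 | 0.553 | 0.548 |
| 0.8 | 0.747 | 0.739 |

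Within-arm rho at 0.6 is also about 0.55. A near-constant shift leaves the ranks within an arm almost intact.

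**4. The AUC itself.** A drop in visits at or above 4 is not a drop in AUC, so the endpoint was simulated: 50 per arm, nine visits, +50 mg/day whenever CGI-S is 4 or more, no drug effect, Mann–Whitney test on the AUC, 1,000 trials per setting. Further assumptions: baseline severity mean 3.5 and SD 0.8, rating error SD 0.5, levodopa lowering severity by 0.15 points per 50 mg, wearable correlation with severity 0.5.

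| Shift | Mean AUC difference | Mann–Whitney rejects | Pooled rho | Rho, istradefylline arm | Arm term, CGI-S on wearable + arm, rejects |
|---|---|---|---|---|---|
| 0 | +0.9% | 6.2% | 0.266 | 0.263 | 5.2% |
| 0.25 | −17.9% | 26.4% | 0.260 | 0.264 | 15.8% |
| 0.5 | −35.4% | 77.4% | 0.260 | 0.279 | 49.4% |
| 0.75 | −51.3% | 98.9% | 0.248 | 0.292 | 85.5% |

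The sampling SD of pooled rho is 0.09 to 0.10, far larger than any movement in the table. The 0.25-point case was repeated with wearable correlation 0.3 to 0.7 and levodopa feedback 0 to 0.3 points per 50 mg. The AUC difference was −16.7% to −18.8%, the rejection rate 26.4% to 29.4%, and pooled rho moved by at most 0.013.

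**5. What an arm coefficient would mean.** Regressing CGI-S on an imperfect severity proxy (correlation r) plus arm, a true benefit d with no rating bias leaves an arm coefficient of about −d(1 − r²). For d = 0.25:

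- r = 0.3: −0.25 × 0.91 = −0.23.
- r = 0.6: −0.25 × 0.64 = −0.16.
- r = 0.8: −0.25 × 0.36 = −0.09.

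The coefficient therefore mixes rating bias with benefit that the wearable misses.

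**The case against.** The strongest defence has four parts.

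- **The correlations are not offered against open-label bias.** Efficacy outcomes and the Discussion present them as a check on CGI-S as the dosing index. Only the wearable sentence in Limitations addresses open-label bias. This stands, and the two statements are judged here against their own separate purposes. The correlations still fail theirs, because association does not show whether decisions at a cut-point would agree.
- **The protocol does not say whether correlations are pooled or by arm, and a detailed SAP is promised before database lock.** This also stands, and the absence of further models from the article is no fault. But coefficients by arm fail in the same way as pooled ones, and an SAP cannot make the stated offset true.
- **The limitation is disclosed, with the word intended, and other scales are compared between groups at each time point.** Discordance between CGI-S and those scales could give a hint. However, no blinded rater is described for them, and the protocol does not present the comparison as a bias check.
- **The numbers rest on assumptions.** They do. At a quarter-point shift the primary test rejects in only 26% to 29% of simulated trials, and the size of any real shift is unknown.

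**Conclusion.** The point holds for two statements. As planned, the wearable does not offset bias in the primary endpoint, and Spearman correlation cannot establish whether dose decisions would differ at CGI-S of 4. Under the stated assumptions, a quarter-point rating shift in one arm would lower the AUC by about 18%, close to the anticipated 20%, with the correlations unchanged within sampling error.

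Three stronger readings are not supported:

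- A reader might infer that rating bias will occur or will explain a positive result. Nothing in the documents shows this, and the shift is hypothetical.
- A reader might infer that the wearable data are useless for this purpose. Only the correlation named is inadequate; the same data can support a between-arm comparison.
- A reader might infer that the arm coefficient from CGI-S regressed on other measures would estimate differential rating. Step 5 of the working shows that it would not.

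The open-label limitation is openly stated. The fault lies in the reassurance attached to it, and it should be corrected before database lock.

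**What to change.** 1. In Limitations, state that the wearable data are supportive only and do not offset bias in the primary endpoint. In the Discussion, remove the inference that correlation establishes the objectivity of the CGI.
2. Compare the wearable measures between arms at Weeks 12, 24 and 36, with 95% CIs.
3. For the question whether dose decisions would differ, tabulate agreement at the threshold by arm, for example CGI-S of 4 or more against PGI-S of 4 or more. Note that PGI-S is also given with knowledge of the arm. Correlations may stay as description.
4. If CGI-S is modelled on the wearable plus arm, report the arm coefficient with its 95% CI as a sensitivity indicator that mixes rating bias with any true benefit the wearable misses. Do not adjust for PGI-S or MDS-UPDRS, which are rated with knowledge of the arm and could absorb the bias sought.

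Cost: wording and a few analyses on data already collected. Downside: precision is low with about 100 patients. At a quarter-point shift the model in item 4 has about 15% to 22% power for wearable correlations of 0.3 to 0.7 (11% to 26% when levodopa feedback is varied at correlation 0.5). A null result is therefore no reassurance, and the report should say so.
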